### Health economic analysis

The primary economic evaluation will follow NICE guidelines [50] and will be a cost-utility analysis (CUA), comparing the incremental costs with incremental QALYs gained, from an NHS and Personal Social Services (PSS) perspective, at 12 months post-operative. Secondary analyses will include taking a societal perspective on costs, and a cost-effectiveness analysis comparing the incremental costs with the primary clinical outcome at 12 months. All analyses will follow a Statistical and Health Economics Analysis Plan.

Resources will be valued using unit cost estimates from national tariffs [51, 52], and liaising with hospital finance departments if necessary. We will assign UK preference-based utility weights [53] to patients’ answers to the EQ-5D-5L questionnaire, and produce unadjusted 1-year QALY scores per arm, using the area under the curve approach [54]. Costs and QALY estimates will then be adjusted for stratification variables, and also for baseline utility [55] for QALYs, using regression methods. Costs and outcomes will be compared between arms to determine dominance, i.e. whether one arm is more effective and costs less than the other. Missing data will be imputed using multiple chained equations [47].

The economic result will be bootstrapped incremental net monetary benefit (INMB) statistics, using a range of societal willingness-to-pay thresholds for a QALY gained. If no arm is dominant, we will compute incremental cost-effectiveness ratios (ICERs) in relation to both outcomes. The primary results will report estimates based on complete datasets with imputed data. We will plot adjusted bootstrapped costs and effects in cost-effectiveness planes and create cost-effectiveness acceptability curves to consider uncertainty around the adoption decision. In sensitivity analysis we will explore sources of methodological and parameter uncertainty, such as costing assumptions.

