### Randomisation

Participants will be randomised with a 1:1 treatment allocation to the intervention group or usual care group 2 weeks after TKR. Prior to randomisation, eligibility criteria will be reassessed through contact with participants and review of operation notes. Randomisation with allocation concealment will be conducted by means of a computer-generated code, administered centrally and communicated via the Internet (through the Bristol Clinical Trials and Evaluation Unit). Randomisation will be stratified by pre-operative function measured by the Lower Extremity Functional Scale [27] (categorised as high or low function based on mean scores from a published study with a similar patient cohort [28]) and recruitment centre (Southmead Hospital or Emersons Green Treatment Centre). Blinding of participants and trial personnel to treatment allocation will not be possible due to the nature of the intervention.

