### Resource use

Resource-use data will be collected from hospital discharge to 12 months post-operative. Resources required to deliver the intervention will be recorded in Case Report Forms by the physiotherapists delivering the intervention. Patient self-report use of services will be collected through patient-completed resource-use questionnaires. The questions will cover the use of additional physiotherapy treatments in hospital and community and other therapies prescribed, readmissions, outpatient visits, GP and nurse visits, medication use and use of social services. To allow for a secondary societal analysis, questionnaires will further collect time off work, leisure activities, private expenditures (e.g. privately paid therapies, travel costs to sessions) and informal care. All participants will be provided with a resource-use log to prospectively fill in resources used to aid them in the completion of the resource-use questionnaires [44].

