### Patient characteristics

Data on socioeconomic status (marital status, living arrangements, ethnicity, educational attainment, working status), medical co-morbidities (Functional Co-morbidity Index [45]), knee symptoms (LEFS, KOOS), quality of life (EQ-5D-5L), and depression and anxiety (HADS) will be collected in the pre-operative questionnaire to allow adjustment for these variables in the analysis. Data on age and gender will be collected by the researcher at recruitment.

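### Costs are adjusted for the stratification variables only while QALYs are also adjusted for baseline utility; using one covariate set for both would be a small, free improvement

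*Protocol article*

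**What the plan says.** The covariates are stated in one sentence of the protocol article, under Health economic analysis: "Costs and QALY estimates will then be adjusted for stratification variables, and also for baseline utility [55] for QALYs, using regression methods". The closing restriction to QALYs keeps baseline utility out of the cost regression. The Randomisation section defines the stratification variables as pre-operative LEFS (high or low) and recruitment centre, so those two are the only covariates named for costs.

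Four other statements bear on the point:

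- **Baseline data.** Under Patient characteristics, socioeconomic status, the Functional Co-morbidity Index, LEFS, KOOS, EQ-5D-5L and HADS "will be collected in the pre-operative questionnaire to allow adjustment for these variables in the analysis".
- **Costs.** Under Resource use: "Resource-use data will be collected from hospital discharge to 12 months post-operative". No pre-operative cost is described.
- **QALYs.** The plan is to "produce unadjusted 1-year QALY scores per arm, using the area under the curve approach".
- **Result.** "The economic result will be bootstrapped incremental net monetary benefit (INMB) statistics", with cost-effectiveness planes and acceptability curves, and cost-effectiveness ratios if neither arm dominates.

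**The concern.** The INMB is the threshold times the QALY difference, minus the cost difference. If patients with worse pre-operative utility have lower QALYs and also higher costs, an arm that starts worse by chance loses on both terms and the two errors add. The stated analysis removes the error from the QALY term. In the cost term it removes only what LEFS category and centre account for.

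What is at stake is how the result of one particular trial reads when baseline utility happens to be unbalanced. The INMB, the planes and the acceptability curves would then carry a residual shift against the arm with the worse start. Incremental cost would also be slightly less precise than the collected data allow. The pre-operative EQ-5D-5L needed to deal with both is already in the QALY model.

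**Working it through.** **Design figure.** The article gives no figure for the economic analysis. Its sample size fixes the number per arm and reproduces: SD 18.4 × 1.12 = 20.608; n = 2 × [(1.96 + 0.842) × 20.608 / 9]² = 82.3, so 83 per arm; 83 / 0.65 = 127.7, so 128 per arm and 256 in total.

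**Step 1: incremental cost alone.** Let rho be the size of the correlation between pre-operative utility and 12-month cost, given the strata. The article gives neither its size nor its sign; I assume 0 to 0.4, with worse utility going with higher cost. By standard covariance adjustment:

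- SE with utility in the cost model ÷ SE without it = √(1 − rho²).
- Shift in incremental cost, in units of its own SE = rho × (imbalance in utility ÷ SE of that imbalance).

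| rho | Cut in SE of incremental cost | Shift at 1 SE imbalance | Shift at 1.96 SE imbalance |
|---|---|---|---|
| 0 | 0% | 0 | 0 |
| 0.1 | 0.5% | 0.10 SE | 0.20 SE |
| 0.2 | 2.0% | 0.20 SE | 0.39 SE |
| 0.3 | 4.6% | 0.30 SE | 0.59 SE |
| 0.4 | 8.3% | 0.40 SE | 0.78 SE |

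These figures do not depend on the number of patients, so they also hold at 83 per arm.

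**Step 2: the INMB.** All values here are assumptions: cost SD £3,000; baseline utility SD 0.25; QALY slope on baseline utility 0.4; residual QALY SD 0.16; threshold £20,000; 128 per arm; true INMB zero. With √(2/128) = 0.125:

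- SE of the adjusted QALY difference = 0.16 × 0.125 = 0.02, worth £400 at the threshold.
- SE of the cost difference without utility = 3,000 × 0.125 = £375.
- SE of the INMB as planned = √(400² + 375²) = £548.
- SE of the INMB with utility in both models = √(400² + 375² × (1 − rho²)): £547 at rho 0.1, £543 at 0.2 and £537 at 0.3. These are reductions of 0.2%, 0.9% and 2.1%. At rho 0.4 it is £527, or 3.8%.

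A simulation of 6,000 trials per setting agrees. The SE of the INMB was:

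| rho | Neither adjusted for utility | QALYs only (as planned) | Both |
|---|---|---|---|
| 0.1 | 615 | 547 | 546 |
| 0.2 | 630 | 547 | 542 |
| 0.3 | 643 | 544 | 532 |

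At a threshold of £30,000 and rho 0.3 the three figures were 853, 713 and 704. The mean INMB was about zero for all three estimators in every setting.

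**Step 3: trials with an unbalanced baseline.** Among simulated trials with more than 1 SE of imbalance in utility (threshold £20,000, rho 0.3), the mean INMB error was £548 with neither side adjusted, £170 as planned and about £0 with both. The plan leaves 170 / 548 = 31% of the error, or 170 / 544 = 0.31 of an INMB standard error. As a check, the average imbalance beyond 1 SE is 0.242 / 0.159 = 1.52 SE, and 0.3 × 375 × 1.52 = £171.

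The simulation has no strata, so rho must be read as the correlation left after LEFS category and centre. That is probably smaller than the raw correlation, because function and utility are likely to be related.

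**The case against.** **The sets differ for a reason.** QALYs are an area under the utility curve, so pre-operative utility can enter the QALY itself and imbalance then carries over mechanically. Costs run from hospital discharge, have no baseline counterpart in the article and have no such link. This stands as a reason to adjust QALYs. It is not a reason to leave utility out of the cost model, where the question is only whether it predicts cost.

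**Any omitted prognostic covariate does this.** Also true. A reader might infer that the planned INMB is biased. It is not: over repeated randomisation all three estimators centre on the true value. The shift is conditional on the imbalance that happens to occur.

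**Costs are not left unadjusted.** A reader might infer that chance imbalance is corrected on one side only. The article adjusts costs for LEFS category and centre, so the gap concerns only imbalance beyond those strata.

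**The detail may be elsewhere.** The article says "All analyses will follow a Statistical and Health Economics Analysis Plan", and that plan is not shown. It may name further cost covariates, so the article does not show that baseline data are wasted. Collecting variables to allow adjustment also does not promise that each enters every model. Still, the article states the two covariate sets outright, so this is a declared choice and can be commented on as such.

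**The gain is small.** This stands and sets the weight of the point.

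**Conclusion.** A minor point that holds as an improvement, not as an error or a contradiction. The stated analysis is valid and, under the assumed values, already captures most of the precision that adjustment for baseline utility can bring to the INMB.

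What remains is a conditional imbalance on the cost side: 0.1 to 0.4 of the SE of incremental cost per 1 SE of imbalance in utility, for rho 0.1 to 0.4. The SE of incremental cost is also about 0.5 to 8% larger than it need be. For the INMB the loss of precision is about 0 to 2% for rho up to 0.3, and about 4% at rho 0.4, at the £20,000 threshold. At rho 0 there is no effect. Every size rests on a correlation, SDs and a threshold that the article does not give. Nothing here supports calling the economic result invalid or the sample size of 256 wrong.

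**What to change.** Replace the covariate sentence, in the article's terms or in the Statistical and Health Economics Analysis Plan, with: *Costs and QALYs will both be adjusted for the stratification variables and pre-operative EQ-5D-5L utility, using the same covariates in both regressions within each bootstrap sample.* If the sponsor prefers to keep different sets, state the reason.

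With identical covariates in both linear regressions, separate least squares gives the same INMB estimate as a single adjusted net-benefit regression. Seemingly unrelated regression then brings no gain in efficiency and need not be required. Adding the Functional Co-morbidity Index is optional.

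The cost is one line of text, fixed before costs are compared between arms so that the covariates are not chosen after the fact. No new data and no more patients are needed, and the planned multiple imputation can cover missing baseline utility.

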## Discussion

This project is a fully powered RCT to evaluate the long-term clinical effectiveness and cost-effectiveness of a novel group-based outpatient physiotherapy intervention following TKR in addition to usual care. The trial includes patients with all levels of functional aspirations, and emphasises the concept of participation in valued activities as a basis for effective and appropriate rehabilitation goals. Our approach aims to both improve function for those patients who may otherwise have unfavourable outcomes, and assist patients who are recovering well to achieve more demanding goals.

A strength of this trial is that the design of the intervention and trial were informed by prior feasibility work [25]. In particular, the feasibility work highlighted the importance of complementing the collection of outcome measures by postal questionnaire with telephone calls to maximise completion rates. This has previously been shown to be an effective strategy with a similar patient population [56], although with the increasing uptake of technology, online questionnaires may be a useful alternative data collection method for future trials. Another strength of this trial is the 12-month follow-up period, which will allow assessment of the long-term impact of physiotherapy on patient outcomes and resource use. However, in addition to patient-reported outcome measures, the trial may have benefitted from the inclusion of more objective measures of function, such as muscle strength or gait analysis, as these capture different dimensions of function [57]. Another limitation of the trial which warrants acknowledgement is the lack of blinding, because of the group-based nature of the physiotherapy intervention. Blinding in trials of physiotherapy is often challenging and only a quarter of physiotherapy trials are blinded [58]. There is a risk that lack of blinding will introduce bias as outcome data will be self-reported by participants who will know which treatment they have been allocated to. A recent meta-epidemiology study found that lack of blinding in physiotherapy trials can lead to an underestimation of the treatment effects compared to trials with blinding, although this was not statistically significant [58]. In addition, while the trial is powered for our primary analysis, other analyses are purely exploratory in nature and will be interpreted as such.

The findings of this trial will provide evidence that has the potential to inform physiotherapy service provision for patients after TKR. Although outpatient physiotherapy has been demonstrated to be effective in improving short-term functional outcomes after TKR [19, 20], it has not been implemented into routine clinical practice. A contributing factor to this is likely to be the lack of evidence about long-term clinical effectiveness and cost-effectiveness of this service. Our study will provide this evidence base for decision-making, inform the development of guidelines for post-discharge care to this growing patient group, and ultimately lead to improved patient outcomes after TKR, with an efficient use of health care resources. This research aims to provide evidence needed to guide decisions by clinicians, policy-makers and patients and inform commissioning of services to ensure all patients receive the best physiotherapy care after TKR.

## Trial status

This trial began patient recruitment in March 2015.

## Abbreviations

CEA, cost-effectiveness analysis; CEAC, cost-effectiveness acceptability curve; CUA, cost-utility analysis; GPs, general practitioners; HADS, Hospital Anxiety and Depression Scale; ICER, incremental cost-effectiveness ratio; INMB, incremental net monetary benefit; KOOS, Knee Injury and Osteoarthritis Outcome Score; LEFS, Lower Extremity Functional Scale; MCID, minimal clinically important difference; MI, multiple imputation; NHS, National Health Service; OA, osteoarthritis; PEP-R, Patient Experience Partnership in Research; PSS, Personal Social Services; QALYs, quality-adjusted life years; RCT, randomised controlled trial; SD, standard deviation; TKR, total knee replacement
